#### b) Patients' clinical outcomes

A consecutive sample of patients consulting with LBP at each participating practice will be recruited in phase 1 for a period of up to 6 months. As each patient consults with LBP at one of the participating GP practices and is assessed, if their GP enters a previously validated back pain Read Code [2] to indicate the reason for consultation as non-specific LBP, a "pop-up" computer prompt will remind them that the patient is eligible to be invited to participate in the IMPaCT Back study. The GP will inform the patient about the study and ask them if they are willing to receive further information by post. On the same computer pop-up screen the GP will record whether the patient is willing to receive further information about the study, in addition to recording their own clinical impression of the patient's risk of poor outcome (low, medium or high risk of poor outcome). The GP will be able to "opt out" of the computer screen pop-up if they consider the patient not eligible for the study. In phase 1, all patients will receive usual primary care, with referral to other services (including physiotherapy) as usual. There will be no subgrouping for targeted treatment in phase 1, or any specific training or additional resources for assessing and managing LBP patients.

Names and addresses of eligible patients will be extracted weekly from the GP practices' electronic databases. These patients will be sent a letter inviting them to participate in the IMPaCT Back study, an information leaflet and a baseline questionnaire, with a pre-paid return envelope. Participants will be asked to record whether they are willing to be contacted again with follow-up questionnaires at 2 and 6 months, and whether they give permission for their medical records to be reviewed. Figure 2 provides a summary of the patient recruitment and follow-up procedures. The patient questionnaire will collect data across the key domains recommended for LBP studies i.e. back specific function, generic health status, pain, psychological distress, work disability and patient satisfaction [36]. Patient outcome measures are summarised in Table 2. As the main focus is the secondary prevention of long-term disability due to LBP, the primary clinical outcomes are change in the key physical and psychological risk factors for chronicity: back-related disability (Roland-Morris Disability Questionnaire (RMDQ) [37]) and catastrophising (sub-scale from the Coping Strategies Questionnaire [38]) at 6 months.

**Figure 2 F2:**
[figure not shown]
Flow chart of IMPaCT Back study patient recruitment and follow-up

**Table 2 T2:** Outcome Measures for Patients

	Domain	Outcome Measures	Time Point (months)
**Primary**	**Back Pain Disability**	Roland and Morris Disability Questionnaire [37]	0, 2, 6
	**Catastrophising**	Catastrophising (from Coping Strategies Questionnaire) [38]	0, 2, 6
**Secondary**	**Kinesiophobia**	Tampa Scale Kinesiophobia [53]	0, 6
	**Bothersomeness**	Bothersomeness [2]	0, 2, 6
	**Anxiety/depression**	Hospital Anxiety and Depression Scale [54]	0, 6
	**Self-efficacy**	Pain Self-Efficacy Questionnaire [55]	0, 6
	**Illness perceptions**	Musculoskeletal Illness Perceptions Questionnaire [56]	0, 2, 6
	**Health-related quality of life**	Short Form 12 (version 2) [57]	0, 2, 6
	**Individualised**	Goal Scaling [58]	0, 2, 6
	**Global change**	Compared to symptoms at baseline	2,6
	**Back Pain**	Pain intensity: 0-10 numerical rating scales of least and average pain in last 2 weeks and current pain	0, 2, 6
		Duration [59]	0
	**Pain elsewhere**	Other body region pain(s)	0
	**Preference-based health utility**	EQ-5D [60]	0, 2, 6
	**Employment details**	Current employment status	0,6
		Current/most recent job title	0,6
		Work loss due back problem	0,6
		Work performance	0,6
	**Patient satisfaction**	With information received	2,6
		With care received	2,6
		Rating of overall results of care	2,6
	**Health care resource use**	Primary care consultations	6
		Secondary care attendances (NHS and private)	6
		Additional health care practitioners (NHS and private)	6
		**Prescription and over-the-counter medicines and treatments**	**6**

#### c) Outcomes for the estimation of cost-effectiveness

Recent UK guidelines for the appraisal of cost-effectiveness require changes in health-related quality of life to be based on public preferences using a choice-based method [39]. The EuroQol EQ-5D, a preference-based measure of health status, meets these requirements [40]. The EQ-5D will be collected via the patients' self-report questionnaires at baseline, 2 months and 6 months. Health care resource use data will be collected through a combination of medical record reviews and the 6 month self-report questionnaire. Data collection will focus on key cost drivers including hospital attendances (inpatient stays, outpatient appointments and any other hospital visits to health care practitioners) within the NHS and private practice, consultations with NHS primary health care providers (e.g. general practitioner, practice nurse), prescribed medications, and over-the-counter treatments. Unit costs assigned to these resources will be obtained from published sources reflecting UK national averages. Across all cost components, data will be collected in a disaggregated format that will enable us to estimate, separately, back pain-related costs and costs for 'other' health problems [41]. To address the societal costs of LBP, beyond those directly applicable to health care provision, data regarding employment status and work absence will also be collected.

For those participants that have given permission for their medical records to be reviewed, data will be collected in order to gain further insight into the referral patterns and behaviours of GPs and the self-reported secondary care episodes reported in the 6 month questionnaire. The medical record data will also allow us to assess the validity of responses to some of the resource use questions within the 6 month questionnaire.

### Phase 2: The subgrouping for targeted treatment system and the quality improvement interventions

In phase 2 we will introduce new care systems within the GP practices and physiotherapy services, using a multi-component quality improvement intervention, to train and support participating health care practitioners to use a new subgrouping for targeted treatment system for LBP patients. Details of the subgrouping tools (19) and the subgrouping for targeted treatment system (20) are already available. Briefly, the key features are:

i) subgrouping tools (simple, electronic and paper-based versions) that classify patients as at low, medium or high risk of poor outcome, to help guide clinical decision-making about treatment and onward referral [19];

ii) subgrouping patients on the basis of potentially modifiable risk factors for chronicity;

iii) targeted treatments in primary care for those classified at low, medium and high risk of chronicity. Within the GP consultation, the targeted treatments include a minimal intervention delivered by GPs (for those patients at low risk of poor outcome), or referral to primary care physiotherapists (for those at medium and high risk of poor outcome). Within the physiotherapy consultation, the targeted treatments include a minimal intervention delivered by physiotherapists (for those patients at low risk of poor outcome at the time of physiotherapy consultation), the use of physical approaches for pain relief and physical function (for those at medium risk), and additional cognitive-behavioural approaches to tackle psychological obstacles to recovery (for those at high risk),

iv) multi-component, quality improvement interventions including educational courses and outreach visits led by opinion leaders, regular audit/feedback and mentoring support for GPs and physiotherapists in addition to organisational support to embed the subgrouping tools within existing IT and clinical management systems.

### The sub-grouping tools and targeted treatment approaches

Two versions of a previously developed and validated subgrouping tool for use in primary care [19] will be used. The tools include key physical and psychological predictors of outcome in LBP. A 6-item computer-based subgrouping tool will be embedded in the EMIS GP computer system, for use in real-time GP/patient consultations. Following completion, patients are categorised as either at low (a score of 2 or less) or high (a score of 3 or more) risk of poor outcome and a recommendation is made about whether or not a referral to physiotherapy is likely to be most appropriate. Patients classified as at low risk of poor outcome are recommended to receive best primary care advice and management by the GP, to include a screen for red flags, reassurance about their good prognosis, the benign nature of their pain, and simple messages and advice about pain relief, appropriate physical activity levels, return to normal activity (including work), avoiding bed rest, appropriate use of pain relieving modalities and the role of further investigations. To reinforce these key messages, a brief information sheet will be given. No onward referral to other services is recommended although patients will be advised to re-consult if symptoms persist. Patients at high risk of poor outcome are recommended to be referred to physiotherapy. The GP and patient are then able to use this recommendation in their decision-making.

A 9-item paper-based version of the subgrouping tool will be used by physiotherapists to categorise patients as at low (a score of 3 or less), medium (score of 4 or more, with fewer than 4 of 5 positive psychological items) or high risk of poor outcome (score of 4 or more, with 4 or 5 positive psychological items) and their subgroup guides the decisions about to treatment. The tool is presented on one side of A4 and is quick to complete and score. The targeted treatment for those at low risk of poor outcome mirrors that provided by GPs (above). For those at medium risk of poor outcome, the physiotherapist will carry out a comprehensive assessment (including a physical assessment) and negotiate an individualised treatment plan which specifically targets the patient's physical prognostic indicators using evidence-based treatments, including advice and explanation, reassurance, education, exercise and manual therapy. The number of treatment sessions is flexible, depending on the needs of the individual patient. Patients at high risk of poor outcome will receive a package of care that addresses psychological obstacles to recovery, in addition to addressing the physical symptoms. This consists of a comprehensive biopsychosocial assessment, including a physical examination and structured identification of individual obstacles to recovery, followed by evidence-based management similar to that described for patients at medium risk of poor outcome but taking a more focused cognitive-behavioural approach. Physiotherapists with additional skills drawn from cognitive-behavioural approaches, to identify and address psychological distress, and enhanced communication skills including motivational interviewing techniques and collaborative goal setting will treat these patients, within the context of an intervention promoting activation, return to normal activities (including work) and management of future recurrences. There is a specific focus on the prognostic indicators identified by the subgrouping tool and the number of treatment sessions is flexible, depending on the needs of the individual patient. Where indicated, patients in the medium and high risk subgroups will be referred onwards for consideration for investigations or secondary care interventions.

### Multi-component quality improvement intervention

We designed our improvement intervention with the view that this could, and should, be reflected on and amended in response to feedback. We reviewed previous studies of implementation research [42] and specifically studies aiming to change the behaviour of health care practitioners in managing LBP [11,26-31,43]. Broadly, these suggested that practitioner-orientated interventions (education, academic detailing, reminders, peer feedback, using educationally influential practitioners) tended to be more effective than those aimed at organisations or patients, that active educational interventions (that include patient examples, practice time, role play, simulation, feedback and review) that directly engage practitioners and multifaceted interventions (combining elements of both educational and organisational interventions) are more likely to be effective. Whilst no single theory of behaviour change was used solely to guide the intervention [44] we used the data from phase 1 on practitioners' attitudes, beliefs and confidence in managing LBP, their treatment orientations from the PABS measure, baseline reported practice (in response to standardised patient vignettes) and actual practice patterns to guide the content of the quality improvement intervention.

Features of the intervention with GP practices and GPs:

a) Two interactive, practice-based group educational sessions referred to as 'Best Practice Updates' for GPs, practice managers and practice nurses. Key messages include diagnostic triage and red flag assessment, the role of imaging, reassurance and advice, activity promotion, sickness certification, return to work and subgrouping for targeted treatment. The subgrouping tool will be introduced and the recommended targeted treatments discussed. Discussion on operational aspects of the study will be included, such as the way in which referral rates to physiotherapy will be monitored regularly so that adequate additional support can be provided, if needed.

b) Embedding the 6-item subgrouping tool in a pop-up computer screen, within the GP EMIS computer systems. The electronic tool is activated whenever a Read Code indicating a non-specific LBP problem is entered by the GP, reminding the GP about the study and prompting completion of the subgrouping tool. A treatment recommendation is automatically generated to support decision-making. We will also offer a paper-based version for those GPs who wish to use it.

c) Educationally influential practitioners (opinion leaders) suggested by GPs (a consultant rheumatologist, a GP with special interests (GPSI) in musculoskeletal problems from the local area) will lead the Best Practice Updates and the GPSI will take a lead role in regular communication with each practice.

d) Support for the initiative by key leads within the organisation (Primary Care Trust), including a lead GP from the Professionals Executive Committee (PEC) and the Chair of the PCT. Two of these individuals will also provide ongoing support for the study as members of the Steering Group.

e) Identification of a volunteer 'link' GP from each practice who will be the key person through which communication about the study will flow. Additional funding for one clinical session per month will support this role.

f) Providing each GP Practice with a study pack containing full details about the IMPaCT Back study.

g) Practice based feedback and individual feedback: Data from phase 1 from GP questionnaires and from actual practice data will be analysed and key findings summarised in the Best Practice Updates, comparing each practice with other participating practices (anonymised) and comparing each GP with other GPs within the same practice (not anonymised). This feedback will be provided in written form in the Best Practice Updates and used to stimulate peer discussion about variation in the management of LBP within each practice.

h) Regular reminders and audit/feedback: we will provide regular email and written communication about the study, and about patient recruitment and use of the subgrouping tool per GP and per practice. The timing of the reminders and regular feedback is anticipated to be monthly, but will be guided by feedback from practices. Reminder stickers about the study will be made available for those practitioners who wish to use them for their computer monitors.

i) Patient case-based discussion: depending on progress and on availability within the practices, we aim to facilitate further group-based practice meetings to focus on patient care, using a patient as an example to show the potential benefits of the sub-grouping for targeted treatment approach in practice. These will be led by a physiotherapist to whom the GP practice refers patients, in order to facilitate patient-based communication between the practice and the associated physiotherapy services.

j) Funding support: As well as the additional funding to support the GP link for the study in each practice (one clinical session per month), each practice will also be given £10 per patient identified, in acknowledgement of the small increase in time that it takes to determine eligibility of patients, to mention the study to the patient, and to complete the 6-item version of the sub-grouping tool.

k) Offers of additional one-to-one or small group educational meetings: each GP practice and GP will be offered further contact with a GP lead in the study team and the study co-ordinator, at regular intervals throughout phase 2 and 3 to review the use of sub-grouping tool, the aims of the study, the targeted treatments or any other study related issue.

Features of the intervention with physiotherapy services and physiotherapists:

a) Pre-training programme reflective activities/reading.

b) Stepped education and training programme consisting of a 3 day course for those delivering the targeted treatment for patients classified as at low and medium risk of poor outcome, including use of the 9-item subgrouping tool, identifying and managing patients with physical obstacles to recovery, best practice for LBP and nerve root pain. A further 6 days of training for those physiotherapists treating patients at high risk of poor outcome. These additional 6 days focus on identifying and managing psychological obstacles to recovery and development of skills through role play, case discussion, audio and video training materials and simulated patients. The training programme is supplemented with comprehensive manuals but is designed to be as experiential, skills-based and interactive as possible and includes discussion of operational aspects of the study. Funding support to cover backfill for time taken out from clinical practice for the purposes of training will be provided and training linked into Continuous Professional Development plans for individuals through negotiation with physiotherapy service managers.

c) Individual feedback and review in monthly mentoring sessions over 12 months following the training programme, the first six months led by the training leads and the second six months by senior physiotherapists and IMPaCT Back participants within the PCT. This was included as ongoing mentoring is likely to be the most effective way of consolidating and further developing knowledge, skills and confidence in the new subgrouping for targeted treatment system.

d) The subgrouping tool integrated within the physiotherapy assessment for patients with back pain and the targeted treatment pathways embedded into the ongoing care pathways for patients.

e) Educationally influential practitioners (opinion leaders) leading the training and mentoring programme, including a consultant clinical psychologist, consultant physiotherapist specialising in pain management, an extended scope physiotherapist in a spinal specialist role, a consultant rheumatologist, a GPSI and a disability advisor.

f) Support for the initiative by key leads within the organisation (Primary Care Trust), including the Chair of the PCT and physiotherapy service managers.

g) Study pack of all study information and documentation.

h) Study newsletter to provide feedback to the participating physiotherapists on the progress of the study.

i) Monthly monitoring of referral rates to physiotherapy and patient waiting times in order to identify and react promptly with funding support to increase physiotherapy response to any increase in demand for the service.

j) Agreed onward care pathways for those patients felt by physiotherapists to require the services of secondary care specialists.

### Phase 3: Observation of clinical practice and patient outcomes following implementation of the new care system

In phase 3, health care practitioners will be able to use the subgrouping tools and the targeted treatment approaches for LBP patients as introduced in phase 2. We will collect data on health care practitioners' back pain-related attitudes and behaviours, patients' clinical outcomes and health care resource use after the introduction of the new subgrouping for targeted treatment system.

#### a) Health care practitioners' attitudes and behaviour and care processes

We will repeat the questionnaire survey of participating GPs and physiotherapists in order to assess changes in their behaviour, attitudes and beliefs about back pain and its management after completion of the training (phase 2) and implementation of the new care systems (phase 3). We will record their reported behaviour in response to the same two clinical case vignettes of real patients with non-specific LBP, and their actual clinical behaviour, from GP medical record reviews and physiotherapy case report forms (in order to compare them with the same data from phase 1).

#### b) Clinical outcomes for patients

A new cohort comprising a consecutive sample of patients consulting with LBP at each participating practice will be recruited in phase 3 for a period of 12 months. The longer timescale in phase 3 is deliberately chosen so that we can study the pattern of use of the subgrouping for targeted treatment systems over time. As time progresses, the use of the new tools and targeted treatment may reduce, as practitioners may tend to go back to previous patterns of practice, and we aim to monitor this.

When the GP enters a relevant back pain Read Code into their clinical computer, the pop-up screen will include the same items as in phase 1 plus the brief (6 item) subgrouping tool, which, once completed, will yield a targeted treatment recommendation for the GP and patient to use to inform their decision-making. Similarly, if the patient is referred to physiotherapy, their assessment at the first visit with the physiotherapist will include use of the subgrouping tool (9 item version), which will yield a recommendation about targeted treatment.

Patient recruitment in phase 3 will be the same as the procedures described for phase 1. Participants who consent to further contact will receive a follow-up questionnaire at 2 months and 6 months (see figure 2). Those patients who reconsult in phase 3, who have previously been invited to take part in phase 1 will not be re-invited. The same patient outcome measures as phase 1 will be used in phase 3 (see Table 2).

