### Patients' eligibility criteria

Male and female adults aged 18 years or over, consulting one of the participating GP practices with non-specific LBP (with or without leg pain). Participants must understand English to a level where they can read the study information leaflet and study questionnaires. Exclusions are those with "red flags" (indicative of possible serious spinal pathology such as cauda equina, inflammatory arthritis, malignancy, infection, fracture); pregnancy-related LBP; conditions which might exclude the patient from physiotherapy treatment (e.g. serious co-morbidity, recent major surgery), patients already receiving physiotherapy treatment for this episode of LBP.

The procedures for recruitment, assessment and treatment are summarised below for each phase of the IMPaCT Back study.

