#### Patients

Scoping work in preparation for this study has provided us with information on rates of consultation and current referral pathways, by which we can assess the expected recruitment and determine the power we will have to detect clinically important changes in patient outcome. The consultation rate for back pain in local general practices ranges from 6-10% annually. We aim to invite 7 GP practices (population of approx 45,000 adults aged 18 years or over) from which we expect at least 2,700 LBP consulters per year. Previous research suggests that approximately 50% of patients will be willing to consent to completing the questionnaires [45]. Based on these figures, we anticipate that within the timeline of the study (across both phases 1 and 3), recruitment of 1000 patients should be feasible.

A difference of 2.5 points in RMDQ [37] change scores is considered to be a minimum clinically important difference [46]. We wish to test the superiority of the subgrouping for targeted treatment system (phase 3) over usual primary care (phase 1) in relation to this 2.5 point difference for those patients in the high and medium risk subgroups, and to test for non-inferiority of the new care system compared to usual care in the low risk subgroup. A weighted sample size (based on the timeline ratio of 1:2 (phase 1: phase 3) of 50 patients (phase 1) and 100 patients (phase 3) is powered at about 80% to detect a 2.5 point difference, assuming a standard deviation of 5 and using a 5% two-tailed significance level. Based on our pilot work, we expect 20% of back pain patients to be classified as at "high-risk" of poor outcome, 40% to be at "medium-risk" and 40% at "low-risk". Thus, our expected study size of 1000 patients will enable us to evaluate this clinical difference across the three risk subgroups, and has 80% power to detect a 'small' effect size of about 0.2, equivalent to a mean difference in RMDQ scores of approximately 1, over the total study population (taking into account 20% loss to follow up).

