#### Clinical outcomes for patients

The primary outcome measures of patient benefit will be back pain-related disability (measured on the RMDQ [37] and pain catastrophising (measured on the catastrophising subscale of the Coping Strategies questionnaire [38] at 6 month follow up. Primary analysis of the patient data will follow the principles of "intention to treat", to compare outcomes of patients in phase 1 (pre-intervention) to those of patients in phase 3 (post-intervention). A "per-protocol" analysis, based on the evaluation of phase 3 patients who were treated with strict adherence to the subgrouping tool allocation rule (versus all phase 1 patients) will be carried out as a secondary comparison. Estimates of treatment effects, i.e. comparative outcomes for phase 1 (pre-intervention) versus phase 3 (post-intervention), with 95% confidence intervals will be calculated using linear regression (for numerical outcomes) and logistic regression (for categorical outcomes). Analyses will be carried out both unadjusted and adjusted for baseline imbalances in certain variables i.e. age, gender and baseline values of key outcomes. Statistical adjustment is necessary as this is an observational, before and after study design, and thus open to the possibility of confounding bias; adjustment will ensure parity of key baseline patient characteristics across phases 1 and 3. Analyses will be carried out at each patient follow up time point (2 and 6 months) for primary and secondary outcome measures; the primary endpoint is 6 months. Analyses will be performed on available data, and on imputed datasets based on the method of multiple imputation [47]. We will use STATA and SPSS for the analyses.

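### Patients invited in phase 1 are barred from phase 3 with no matching exclusion in phase 1, so recurrent consulters are partly depleted from the phase 3 cohort only, and the stated adjustment does not cover this

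*Protocol article*

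**What the plan says.** The phase 1 cohort is a consecutive sample of low back pain consulters that "will be recruited in phase 1 for a period of up to 6 months" (Phase 1, b) Patients' clinical outcomes). Under Patients' eligibility criteria, the only exclusion tied to the history of the episode is "patients already receiving physiotherapy treatment for this episode of LBP". An earlier GP consultation for back pain does not exclude anyone.

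The phase 3 cohort (Phase 3, b) Clinical outcomes for patients) is also called consecutive and "will be recruited in phase 3 for a period of 12 months". That section states that "Patient recruitment in phase 3 will be the same as the procedures described for phase 1", but adds one rule that phase 1 lacks: "Those patients who reconsult in phase 3, who have previously been invited to take part in phase 1 will not be re-invited". The rule covers everyone invited, not only those who took part.

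Under Data analysis, Clinical outcomes for patients, the phases are compared by regression, unadjusted and "adjusted for baseline imbalances in certain variables i.e. age, gender and baseline values of key outcomes". The same paragraph calls adjustment necessary because the design is open to confounding, and expects it to bring parity of key baseline characteristics. Pain duration is collected at baseline (Table 2) but is not in the named set. Nor is prior consultation. The Discussion lists outside influences, practitioner change and Hawthorne effects as limitations, but not this difference in selection.

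**The concern.** A phase 1 invitee is affected by the bar only on consulting again in phase 3. The bar therefore acts selectively on people with persistent or recurrent pain, and on the intervention cohort alone. The window lengths act in the same direction: a 6-month window holds a larger share of frequent consulters than a 12-month window does.

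The phase contrast is the only estimate of effect, and the cost-utility analysis uses it too. If recurrent consulters improve less by 6 months, their depletion from phase 3 moves the contrast towards the new system, and a larger sample does not reduce that. Adjusting for baseline RMDQ and catastrophising helps. It may not be enough, because two patients with the same score, one with new pain and one with long-standing pain, can be expected to change differently.

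**Working it through.** **The plan's own figures.** With 1,000 patients and 20% loss, 800 are analysed, or 267 and 533 at 1:2. At SD 5 the standard error of the phase difference is 5 × √(1/266.7 + 1/533.3) = 0.375. The difference detectable with 80% power at two-sided 5% is (1.96 + 0.84) × 0.375 = 1.05 points, an effect size of 0.21. This agrees with the stated effect size of about 0.2 and difference of approximately 1 point. The subgroup calculation (50 and 100 patients, 2.5 points, SD 5) gives 82%, against about 80% stated. The sample size is not in question; it supplies the yardstick of about 1 point.

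**Inputs for the bias**
- From the protocol (Sample Size, Patients): about 45,000 adults, "from which we expect at least 2,700 LBP consulters per year", so 2,700/45,000 = 6% a year.
- Assumed: a fraction p = 1-3% of adults are frequent consulters, at λ = 1-3 consultations a year. The rest consult at a low rate that brings the annual total to 6%.
- Assumed: a fraction c = 50-100% of phase 1 consulters are invited.
- Assumed: frequent consulters are 2 or 4 RMDQ points worse at 6 months.

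**Formulas** (Poisson consultations at yearly rate λ)
- Chance of entering phase 1: 1 − exp(−λ/2)
- Chance of entering phase 3 without the bar: 1 − exp(−λ)
- Chance of entering phase 3 with the bar: [1 − exp(−λ)] × [1 − c(1 − exp(−λ/2))]
- Bias = difference in the share of frequent consulters × RMDQ gap

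**Lowest corner** (p = 1%, λ = 1, c = 50%)
- Frequent consulters supply 0.01 × 0.632 = 0.0063 of the 0.06, so the low rate is −ln(1 − 0.0537/0.99) = 0.0557.
- Share in phase 1: 0.00394/(0.00394 + 0.0272) = 12.6%.
- Share in phase 3 without the bar: 0.0063/0.06 = 10.5%.
- Share in phase 3 with the bar: 0.00508/(0.00508 + 0.0529) = 8.8%.
- At a 2-point gap, on unrounded shares: bar alone 0.036; bar plus windows 0.078.

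**Highest corner** (p = 3%, λ = 3, c = 100%)
- Frequent consulters supply 0.03 × 0.950 = 0.0285, so the low rate is −ln(1 − 0.0315/0.97) = 0.0330.
- Share in phase 1: 0.0233/(0.0233 + 0.0159) = 59.5%.
- Share in phase 3 without the bar: 0.0285/0.06 = 47.5%.
- Share in phase 3 with the bar: 0.0064/(0.0064 + 0.0310) = 17.0%.
- At a 2-point gap: bar alone 2 × (0.475 − 0.170) = 0.61; bar plus windows 2 × (0.595 − 0.170) = 0.85.

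These corners bound the bias over all 18 combinations of p = 1, 2, 3%, λ = 1, 2, 3 and c = 50, 100%:

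| RMDQ gap | Bar alone | Bar plus unequal windows |
|---|---|---|
| 2 points | 0.04-0.61 | 0.08-0.85 |
| 4 points | 0.07-1.22 | 0.16-1.70 |

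All entries are before baseline adjustment.

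**Cross-check on the bar by a different route.** Pro rata there are 1,350 phase 1 consulters against 2,700 in phase 3, so the bar can remove at most about 50% of phase 3 consulters. Assume 50-100% are invited and 20-50% of those reconsult. The share removed is then r = 1,350 × invited × reconsulting / 2,700, or 5-25%. With removed patients d = 1-4 points worse (assumed), the bias r × d is 0.05-1.0. A middle case, r = 17.5% and d = 2, gives 0.35 points. Against a standard error of 0.375, that raises the two-sided rejection rate with no true effect from 5% to 15%. If baseline adjustment removed half (assumed), the bias would be 0.175 and the rate 7.5%.

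**The case against.** A reader might infer that phase 3 will look better even if the new system does nothing. The protocol does not support that. It gives no reconsultation rate and no prognosis for reconsulters. Its Background also weakens consultation as a marker of persistence: many patients stop consulting within three months, yet 60-80% report pain or disability a year later. Many persistent sufferers therefore never meet the bar. Depletion is partial in any case, since people who consulted only before phase 1 or between the recruitment windows are not barred. This stands: the direction is an inference and the size is unknown.

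A reader might also charge the whole shift to the bar. Part comes from the longer phase 3 window, which was chosen deliberately to follow use of the system over time.

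The figures are unadjusted, whereas the plan adjusts for baseline outcome values and frames the primary outcomes as change. The bias left in the adjusted analysis will be smaller by an unknown amount. The Discussion concedes that a before-and-after design may not allow definitive attribution. The rule also has a sound purpose: it keeps the same person out of both cohorts, as ordinary regression requires.

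None of this removes the asymmetry. The named covariates include neither duration nor consultation history, and the general caveat concerns outside influences, not a selection rule built into the design.

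**Conclusion.** The concern holds in a limited form. The cohorts are selected by different rules, recurrent or persistent consulters are partly depleted from phase 3 only, and the named adjustment set does not address it. The phase contrast can therefore favour phase 3 with no true effect, provided that those patients have a worse 6-month course at the same baseline score. The size ranges from negligible to an appreciable part of the roughly 1-point design target; before adjustment it exceeds that target only at the extreme of the assumed inputs with a 4-point gap. The consultation pattern, invitation coverage and RMDQ gap are all assumptions. This should be fixed, with moderate confidence. It does not invalidate the design.

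**What to change.** Keep the no-re-invitation rule. Re-inviting reconsulters would put the same people in both cohorts. Then:

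- Add baseline pain duration, already in Table 2, to the adjusted model for every phase contrast.
- Among patients who consent to record review, flag any earlier Read-coded low back pain consultation over a look-back of the same length and lag in both phases. Run one sensitivity analysis that adjusts for the flag and one restricted to unflagged patients in both phases.
- Report how many phase 3 consulters were barred.
- Name the selection difference among the limitations.

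The cost is a record query, some analysis wording and lower precision in the restricted analysis. Under the assumed model with every prior consultation flagged, restriction drops about 7% of phase 1 patients (0.126 × 0.393 + 0.874 × 0.027) to 47% (0.595 × 0.777 + 0.405 × 0.016). It also leaves a window-length residual of about 0.03-0.16 points at a 2-point gap. For both reasons, and because record consent limits who can be flagged, restriction belongs in a sensitivity analysis and should not replace the main contrast.
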